### Data and Statistical Analysis

While conducting the given tasks, the qualitative data collected via the think-aloud method will be transcribed, coded, and analyzed according to the grounded theory [41,42], a classical qualitative data analysis method. This data analysis has not begun yet because data are still being collected. Combined analysis of discourse [30], video recordings of the study sessions, and screen activities will be conducted. The main components or patterns that we will focus on during analysis include potential nonverbal steps, sequential ordering among different components (such as prioritization of the use of either experience or data) across groups, seeking and processing evidence, analyzing data, generating inferences, making connections, formulating a hypothesis, searching for information needed to generate research hypotheses, and so forth. Ideally, based on video analyses and observations, we plan to develop a framework for the scientific hypothesis–generation process in clinical research, which is guided by secondary data analytics. Similar frameworks exist in education and learning areas [43], but do not currently exist in the field of clinical research.

The outcome variable used is based on the participants’ performance in research hypothesis–generation tasks. The performance is measured by the quality (eg, significance and validity) and quantity of the research hypotheses generated through the tasks and the average time to generate 1 research hypothesis. At least three clinical research experts will assess each hypothesis using the scientific hypothesis assessment metrics that were developed for this study. The metrics include multiple items, each on a 5-point Likert scale. The details of the metrics are described in the Instrument Development section.

The data will be analyzed with a 2-tailed factorial analysis. We calculated the required sample size in G*Power 3.1.9.7 for a 2-way ANOVA. The sample size was 32 based on a confidence level of 95% (α=.05), effect size f=0.5, and power level of 0.8 (β=.20).

In Study 1, we will use descriptive statistics to report how many hypotheses were generated, average time spent per hypothesis, and how many hypotheses were evaluated for each participant. A 2-way ANOVA will be used to examine the main effects of VIADS and experience, as well as the interaction effect of the 2 factors. In the ANOVA, the outcome variable is the expert evaluation score. The follow-up survey data will be analyzed using correlations to examine the relationship between participants’ self-rated creativity, the average time per hypothesis generation, the number of hypotheses generated, and the expert evaluation score. The SUS will be used to assess the usability of VIADS. Qualitative data from the SUS surveys will be used to guide revisions of VIADS after Study 1. Descriptive statistics will also be used to report the answers to other follow-up questions.

A *t* test will be conducted to determine whether the revised VIADS improves the performance of research hypothesis generation in Study 2.

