### Study Design

Study 1 tests all 3 study hypotheses. If the study hypotheses are supported in Study 1, we will conduct a follow-up study (Study 2) to examine whether and how the efficiency or quality of research hypothesis generation may be improved or refined.

We will use the think-aloud method to conduct the following tasks: (1) observe the research hypothesis–generation process; (2) transcribe data, and analyze and assess if VIADS [22] and different levels of experience of clinical researchers influence the process; and (3) assess the interactions between VIADS (as an example of a secondary analytical tool) and the experience levels of the participants during the process. Figure 3 summarizes the Study 1 and Study 2 procedures.

#### Study 1

Experienced and inexperienced clinical researchers conduct research hypothesis–generation tasks using the same secondary data sets. The tasks are captured to describe participants’ research hypothesis–generation processes when guided by analysis of the same data sets. VIADS is also used as an example of a secondary data analytics tool to assess participants’ research hypothesis–generation processes. Accordingly, 2 control groups do not use VIADS, while 2 intervention groups do use it.

A pilot study, Study 0, was conducted in July and August 2021 for each group to assess the feasibility of using the task flow, data sets, screen capture, audio and video recordings, and study scripts. In Study 1, 4 groups are utilized. Table 3 summarizes the study design and participants in each group. The 4 groups will be compared in order to detect the primary effects of the 2 factors and their interactions after completing Study 1. After recruitment, the participants are separated into experienced or inexperienced groups based on predetermined criteria. Then, the participants are randomly assigned to a group that uses VIADS (3-hour session, with 1 hour to conduct VIADS training) or does not use VIADS (2-hour session) via block randomization.

**Table 3 table3:** Design of Study 1 for assessment of the hypothesis–generation process in clinical research.

Variable	Number of experienced clinical researchers	Number of inexperienced clinical researchers
Not using VIADS	8 (Group 1)	8 (Group 2)
Using VIADS	8 (Group 3)	8 (Group 4)

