### Lessons Learned

We learned some important lessons while designing and conducting this study. The first lesson involved balancing the study design (straightforward or complicated) and conducting the study (feasibility). During the design stage, we were concerned that the 2×2 study design was too simple, even though we know it does not negatively impact the value of the research. We simply considered experience levels and whether the participants used VIADS in a very complicated cognitive process. However, even for such a straightforward design, only 1 experienced clinical researcher has volunteered so far. Thus, we will first focus on inexperienced clinical researchers. Even for study sessions involving inexperienced clinical researchers, considerable time is needed to determine strategies for coding and analyzing the raw data. In order to design a complicated experiment that answers more complex questions, we must consider balancing practical workload, recruitment reality, expected timeline, and researchers’ desire to pursue a complex research question.

Recruitment is always challenging. Many of our panel invitations to clinical research experts either received no response or were rejected, which significantly delayed the study timeline, in addition to the effects of the COVID-19 pandemic. Furthermore, the IRB approval process was time-consuming, delaying our study when we needed to revise study documents. Therefore, the study timeline includes the IRB initial review and rereview cycles.

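### The stated inputs for the 2-way ANOVA need 34 participants, not 32; and the power statement names no contrast, although f=0.5 means a 2 SD difference of differences for the interaction

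*Protocol article*

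**What the plan says.** The protocol article, Data and Statistical Analysis, names the software and the model ("We calculated the required sample size in G*Power 3.1.9.7 for a 2-way ANOVA") and then gives the result: "The sample size was 32 based on a confidence level of 95% (α=.05), effect size f=0.5, and power level of 0.8 (β=.20"). The same section describes the test as two-sided: "The data will be analyzed with a 2-tailed factorial analysis". It adds that the ANOVA outcome is the expert evaluation score, and that the model will examine the effect of VIADS, the effect of experience and their interaction.

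Table 3 in the Study Design section places 8 participants in each of four cells. On purpose, that section says: "The 4 groups will be compared in order to detect the primary effects of the 2 factors and their interactions". The third study hypothesis in the Introduction is that experience and tool use interact, and the Study Design section says that Study 1 tests all three hypotheses.

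The article does not say which of the three effects f=0.5 refers to. It gives no standard deviation for the expert score, no expected score difference, and no reason for the chosen f.

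**The concern.** Two things are wrong with the sample-size sentence.

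First, it is specific enough to be rerun, and the rerun does not give 32 at 80% power.

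Second, a single f stands behind three tests that do not mean the same thing on the score scale. A reader will take 80% as the power of the planned ANOVA, including the interaction test that carries the third hypothesis. The f that yields about that power corresponds, for the interaction, to an effect twice as large in SD units as for a main effect.

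What is at stake is how a non-significant interaction will be read. If 80% power is taken at face value, such a result looks like fair evidence that VIADS works alike in both experience groups. With 32 participants it would be weak evidence unless the interaction were very large. The Study Design section also makes Study 2 conditional, in general terms, on the study hypotheses being supported, and the interaction is one of them.

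**Working it through.** **Inputs, all from the protocol article**
- α = 0.05, two-sided; power 0.80; f = 0.5; total N = 32 (Data and Statistical Analysis).
- Four cells of 8 (Table 3).
- Each of the three effects in a 2×2 layout has numerator df = 1.
- Assumed here: one score per participant, a common within-cell SD, equal cells.

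**Power formula.** For a fixed-effects ANOVA, power = P(F′ > Fcrit), where F′ is noncentral F with df 1 and N − 4 and noncentrality λ = N·f². Fcrit is the 95th percentile of the central F with the same df.

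**The stated figure, and the sizes above it, at f = 0.5**

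| N | df2 | λ = 0.25·N | Fcrit | Power |
|---|---|---|---|---|
| 32 | 28 | 8.00 | 4.196 | 77.9% |
| 33 | 29 | 8.25 | 4.183 | 79.3% |
| 34 | 30 | 8.50 | 4.171 | 80.5% |
| 36 | 32 | 9.00 | 4.149 | 82.9% |

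The smallest N reaching 80% is 34. The smallest with equal cells is 36 (9 per cell). A simulation of the interaction at f = 0.5 with 8 per cell gave 77.8%, in agreement with the formula.

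**Can 32 be recovered another way?** Treating the comparison as two groups (df2 = N − 2) still needs 34. Numerator df of 2 needs 42, and of 3 needs 48. A normal approximation for two means 1 SD apart does return 32: n per level = 2 × (1.960 + 0.842)² / 1² = 15.7, rounded up to 16, so 32 in total. That is not the ANOVA calculation that the article says was run.

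**Size of the main-effect shortfall.** 80.0 − 77.9 = 2.1 percentage points. At N = 32, 80% power is reached at f = 0.513.

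**What f = 0.5 means for each effect** (f is the root mean square of the cell deviations divided by the SD)
- Main effect with marginal difference Δ: every cell deviates by ±Δ/2, so f = Δ/(2 SD). With f = 0.5, Δ = 1 SD.
- Interaction with difference of differences D: every cell deviates by ±D/4, so f = D/(4 SD). With f = 0.5, D = 2 SD. For a full 80% at N = 32, D = 4 × 0.513 = 2.05 SD.

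**Interaction power for a smaller D.** If D = 1 SD, then f = 1/4 = 0.25, λ = 32 × 0.0625 = 2, and power = 27.7%. Reaching 80% at that f would take 128 participants. An intermediate f = 0.40 (D = 1.6 SD) gives 58.9%.

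**Precision of the interaction estimate.** SE(D) = SD × √(4/8) = 0.707 SD. The critical t is √4.196 = 2.048. The 95% confidence interval therefore has a half-width of about 2.048 × 0.707 = 1.45 SD. An observed D of zero would still leave differences of differences above 1 SD, in either direction, inside the interval.

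**The case against.** **The gap between 32 and 34 is trivial.** It is two participants and about two points of power, and a common approximation gives exactly 32. This stands as far as materiality goes: for main effects it changes no decision and calls for no extra recruitment. It does not make the sentence correct, because the article names the ANOVA routine and its inputs, and those do not yield 80% at 32.

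**The article never claims 80% power for the interaction.** True, it names no contrast. But this is the only power statement, it is made for the 2-way ANOVA as a whole, and the interaction is one of that model's three stated tests. Leaving the contrast open is the defect.

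**A condensed article may leave the rationale for f to the full protocol.** That is fair, and the missing rationale is not the main charge. The charge is that the statement as printed reads alike for effects that differ by a factor of two in SD units.

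**Stronger readings do not stand.**
- A reader might infer that a 2 SD interaction is implausible, or that the third hypothesis can hardly be tested. The article gives no SD and no expected effect, so neither can be shown. A 2 SD difference of differences would arise, for example, if VIADS helped one group by 1 SD and hindered the other by 1 SD, and the Initial Observations section does report that VIADS training added cognitive load.
- A reader might take the remark in Lessons Learned that "only 1 experienced clinical researcher has volunteered so far" as showing that the power figure has already failed. That is an openly reported interim status, and recruitment at all levels was continuing. Power for some smaller experienced group would rest on an invented enrolment figure and says nothing about how 32 was derived.
- A reader might tie the whole Study 2 decision to the weak interaction test. The explicit branches in the Study 2 section turn on the two main effects; only the general condition in the Study Design section takes in the interaction.

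**Conclusion.** The point holds in two parts of unequal weight.

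- **Minor:** the stated inputs need 34 participants (36 balanced), and the planned 32 gives 77.9% rather than 80% for a 1-df effect at f=0.5.
- **More important:** the power statement does not say which effect it covers. It is about right for a 1 SD main effect. For the interaction the same figure requires a 2 SD difference of differences, which is very large and unexplained, and power for a 1 SD difference of differences is about 28%.

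The 28% is conditional on that illustrative 1 SD value and is not a forecast; the article offers nothing from which to choose a value. The results also assume one score per participant, equal cells of 8 and a common SD. The planned size itself does not have to change.

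**What to change.** Keep 32 participants and replace the sample-size sentence with something like:

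> *32 participants (8 per cell) give 78% power for each main effect at f=0.5 (a 1 SD difference), two-sided α=.05. For the interaction the same power requires a 2 SD difference of differences; power is about 28% for a 1 SD difference of differences.*

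Add one sentence saying that the interaction will be reported as an estimate with its 95% confidence interval, and that a non-significant result will not be interpreted as absence of interaction.

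The cost is wording only, with no extra participants and no change to the analysis model. The stated power becomes slightly less favourable for the main effects and plainly less favourable for moderate interactions. The error does not require a new primary contrast or an added fallback analysis.

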**Results:**

Data collection for this study began in July 2021. Recruitment uses a brief online survey. The preliminary results showed that study participants can generate a few to over a dozen scientific hypotheses during a 2-hour study session, regardless of whether they used VIADS or other analytics tools. A metric to more accurately, comprehensively, and consistently assess scientific hypotheses within a clinical research context has been developed.

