**Figure 2 figure2:**

Development process for metrics to evaluate research hypotheses in clinical research.

The performance of scientific hypothesis–generation tasks will be measured using metrics that include the following qualitative and quantitative measures: validity, significance, clinical relevance, feasibility, clarity, testability, ethicality, number of total scientific hypotheses, and average time used to generate 1 scientific hypothesis. In an online survey, the panel of clinical research experts will assess the generated research hypotheses based on the metrics we have developed.

A survey (Multimedia Appendix 1) is administered for the first 4 groups at the end of the research hypothesis–generation study sessions (Figure 3). The groups that use VIADS also complete a modified System Usability Scale (SUS) questionnaire (Multimedia Appendix 2) evaluating the usability and utility of VIADS. The follow-up or inquiry questions and parameters generated during the think-aloud process used in Study 1 (Figure 3) are as follows:

What are the needed but currently unavailable attributes that would help clinical researchers generate research hypotheses? The question is similar to a wish list of features facilitating research hypothesis generation.Follow-up questions clarify potential confusion during the think-aloud processes or enable meaningful inquiries when unexpected or novel questions emerge during observations [38]. However, these questions have been kept to a minimal level to avoid interrupting clinical researchers’ thinking processes. This method complements the data from the think-aloud video captures.Can the list of items in Multimedia Appendix 3, which has been compiled from traditional clinical research textbooks [1-3,8,39] on scientific hypothesis generation and research question formulation, facilitate clinical researchers’ research hypothesis generation when guided by secondary data analysis?

A survey will be developed based on the comparative results of the first 4 groups and administered at the end of Study 2. The identified differences from Study 1 will be the focus of the survey to determine whether these differences are helpful in Study 2.

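### Correlations planned across the 2×2 sample without mention of group can arise from group differences alone, and the time–number pair may be negative by construction

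*Protocol article*

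**What the plan says.** The Data and Statistical Analysis section gives Study 1 a 2-way ANOVA with VIADS, experience and their interaction. It adds: "In the ANOVA, the outcome variable is the expert evaluation score". The next sentence turns to the survey: "The follow-up survey data will be analyzed using correlations to examine the relationship between" four variables. They are listed there as "self-rated creativity, the average time per hypothesis generation, the number of hypotheses generated, and the expert evaluation score". It does not say whether these correlations are pooled or adjusted for group, and it gives no test, significance level or confirmatory role for them.

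Three other places bear on the point:
- Study Design, Study 1, says of the four groups of 8: "The 4 groups will be compared in order to detect the primary effects of the 2 factors and their interactions". The Instruments section has the follow-up survey given after every session in all groups, so the correlation data come from all four cells.
- Instrument Development lists "average time used to generate 1 scientific hypothesis" among the performance measures, beside the number of hypotheses. No formula for the average is given.
- On task time, Study 1 says a participant "uses VIADS (3-hour session, with 1 hour to conduct VIADS training) or does not use VIADS (2-hour session"). The abstract reports that "study participants can generate a few to over a dozen scientific hypotheses during a 2-hour study session".

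**The concern.** There are two separate mechanisms.

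**Group mixing.** The study expects its groups to differ on performance, which the article measures by quality, quantity and average time. If two variables both differ in mean between cells, pooling the cells produces a correlation between them even when, inside each cell, a participant's value on one says nothing about the other.

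**Shared divisor.** If average time is total task time divided by the number of hypotheses, one variable of that pair contains the other as its divisor. With task time limited to about 2 hours in both arms (3 − 1 = 2 with VIADS, 2 without), the pair must move in opposite directions.

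At stake is the interpretation of a secondary analysis. A statement that faster participants produce more, or that more creative participants score higher, could be published as a finding about participants when it reflects the design or arithmetic.

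**Working it through.** **Plan's own figure.** The article gives no figure for the correlations. Its sample size is 32, from α=0.05, f=0.5 and power 0.80 for the 2-way ANOVA. For a main effect with 1 numerator degree of freedom, f=0.5 is a difference of d = 2f = 1 SD between the two levels. The normal approximation then gives 16 per level, 32 in total. The noncentral F with λ = f²N = 0.25 × 32 = 8 gives power 0.779 at N=32 and a minimum N of 34. So 32 is approximately reproduced, and reading f=0.5 as a 1 SD shift fits the plan.

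**Group mixing, by formula.** Take two variables with within-cell SD 1 and within-cell correlation 0. A factor with two equal levels that shifts a variable by d = 2f adds d²/4 = f² to its variance. If the factor shifts both variables, it adds f² to their covariance. With k factors acting in the same direction:

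r = k·f² / (1 + k·f²)

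- One factor, f=0.5: 0.25/1.25 = 0.20.
- Two factors, f=0.5: 0.50/1.50 = 0.33.
- One factor, f=0.25: 0.0625/1.0625 = 0.06. Two factors: 0.125/1.125 = 0.11.
- Opposing (one factor moves the two variables the same way, the other moves them apart by the same amount): f² − f² = 0.

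**Group mixing, by simulation.** 20,000 studies, four cells of 8, two-sided test of Pearson's r at 0.05. The pooled test has 30 df. The adjusted test is the partial correlation given the four cells, with 32 − 2 − 3 = 27 df.

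| Shift in both variables | f | Mean pooled r | Pooled: significant | Adjusted: significant |
|---|---|---|---|---|
| One factor | 0.25 | 0.06 | 6.4% | 5.3% |
| One factor | 0.40 | 0.14 | 11.4% | 4.7% |
| One factor | 0.50 | 0.21 | 20.7% | 5.1% |
| Two factors, same direction | 0.25 | 0.12 | 9.3% | 5.3% |
| Two factors, same direction | 0.40 | 0.25 | 28.0% | 5.0% |
| Two factors, same direction | 0.50 | 0.34 | 49.8% | 5.3% |
| Two factors, opposing | 0.25 | 0.00 | 4.7% | 4.9% |
| Two factors, opposing | 0.40 | 0.00 | 4.2% | 5.1% |
| Two factors, opposing | 0.50 | 0.00 | 3.8% | 5.4% |

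Formula and simulation agree, and adjustment restores about 5% throughout.

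**Shared divisor.** Assumptions: average time = T/K, with total time T independent of the number K. K is either uniform on 3–15 or 1 + Poisson(6), chosen to match the reported range of a few to over a dozen. Mean correlation of K with T/K:

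| Total time T (minutes) | K uniform 3–15 | K = 1 + Poisson(6) |
|---|---|---|
| Fixed at 120 | −0.91 | −0.88 |
| Uniform 60–120 | −0.85 | −0.79 |
| Uniform 30–120 | −0.74 | −0.66 |

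Rejection is 99.6–100%, pooled or adjusted, so group adjustment does not help here. Two counter-checks limit the claim. If average time is drawn independently of the number, mean r is 0.00 and rejection 5.0%. If T/K is correlated with an independent score, rejection is about 5%, so the divisor alone does not distort that pair.

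**The case against.** The strongest reply is that most of this rests on silence in a condensed article. The plan does not say pooled, and the form of a secondary correlation can reasonably sit in a fuller document. That stands as a limit on wording: pooling is the natural reading of plain correlations set beside a factorial ANOVA, but it is not stated.

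Other parts also stand:
- The sentence is about survey data and can be read as self-rated creativity against each of the other three variables. On that reading, time and number are not paired.
- Sessions are recorded on screen and video, so time per hypothesis could be measured directly and not by division.
- The 50% figure needs both factors to shift both variables by 1 SD in the same direction. The plan attaches f=0.5 only to the ANOVA, whose outcome is the expert score. No study hypothesis concerns self-rated creativity.
- Pooled and within-group correlations answer different questions, so a pooled value is not an error if it is labelled as such.

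A reader might go further and infer that all the planned correlations are spurious. The documents do not support this: the divisor touches one of up to six pairs, and group mixing needs both variables to shift with the design without cancelling. A reader might also infer that time and number would give nearly the same correlation with any third variable. With a strong negative link between them, the signs would tend to be opposite.

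What the reply does not remove is that, followed as written, the analysis mixes four cells that the study expects to differ, and lists a pair that may be tied by arithmetic.

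**Conclusion.** The point holds as a modest improvement to a secondary analysis. Pooled correlations over the 2×2 sample can reach significance with no relationship within groups: about 21% of studies if one factor shifts both variables at f=0.5, about 50% if both factors do so in the same direction, 6–9% at f=0.25, and no inflation if the shifts oppose. These figures assume pooling, the full 32 participants in equal cells, a test at 0.05, and an f=0.5 shift in the second variable that the plan does not state.

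The number–time pair is uninformative if average time is total time over number and the pair is correlated at all. The size, −0.66 to −0.91, depends on the assumed counts and times.

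A reader might take this as a threat to the main result. It is not: the ANOVA models both factors, and the decision on Study 2 rests on group differences and not on these correlations.

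**What to change.** 1. State that the main version of each correlation is the partial correlation given VIADS, experience and their interaction, with the pooled value beside it as description.
2. Define average time per hypothesis: which time is counted, and whether it is total time divided by number or timed directly for each hypothesis.
3. Omit the number–time correlation, or label it descriptive only.

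The change is one of wording, on data already planned for collection. It costs 3 degrees of freedom (30 to 27). The smallest |r| significant at 0.05 is t/√(t² + df), which rises from 2.042/√(4.17 + 30) = 0.349 to 2.052/√(4.21 + 27) = 0.367.
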